##### Passive monitoring

The HappyMums application will ask users for permission to access in-built smartphone sensors, in order to gather data pertinent to physical activity, sociability and phone usage. A detailed description of each data type can be found in table 2.

**Table 2 T2:** Description of data types collected by passive monitoring in the HappyMums application

Passive data type	Description
Pedometer	As a measure of physical activity, number of steps per hour and day will be counted.
GPS	As a measure of participant’s mobility, GPS acquisition in the HappyMums app will be done by adding a random delta of distance (from 10 km to 100 km) to the raw GPS position of the device. The delta will be generated directly on the device, so it will not be known by the backend service and, in this way, guaranteeing anonymisation. Anonymised GPS data will be stored and used to extract different features describing mobility habits, like: number of places visited, time spent in each place, distance travelled and entropy (measurement of uncertainty of data that in behavioural analysis may describe dispersion or clustering of data in a geographical region, ie, high mobility vs limited one).
Accelerometer	As a measure of sleep and activity, this will collect information on phone movement, including shaking, tilting, swinging and rotating.
Light sensor	As a proxy measure for sleep, the app will collect data on the ambient light of the room in which the phone is located.
Screen status	To give information on sleep and phone usage, the app will collect data on when the phone is locked, unlocked and in use.
Call logs	As a measure of sociability, the app will collect information on call frequency, duration and number of missed calls. This will not include specific contact names or phone numbers.
App usage	As a second measure of sociability, the app will be capable of measuring usage of types of apps, for example, time spent using social media applications. The app will not collect the name/reference of the specific apps used.

GPS, Global Positioning System.

##### Mum-to-be Mental Wellbeing course

Users of the application will have access to a library of information and resources, the ‘Mum-to-be Wellbeing course’, which contains information on 21 various topics related to the perinatal period (eg, ‘All about mood: let’s talk about depression in the perinatal period’, ‘Let’s relax: how to relax the body’, ‘The baby: Fetal movements and bonding with your baby’) and has been curated by perinatal experts from the consortium. Further details about the chapters are in online supplemental material. The material is split into content for each of the three trimesters and will be made available to users as they enter their relevant trimester. The main purpose of this course within the HappyMums app is to increase the motivation to use the app and provide relevant verified information about pregnancy and mental health to pregnant women.

##### Data visualisation

The mobile application will provide a space for the visualisation of some data types, for the user to track their own data. This will include information like time spent active during the day and sleep quality from the questions, as well as phone usage (calls, apps categories) or mobility (ie, deltas in GPS data).

### Risk factor assessment

The HappyMums app study aims to build a holistic picture of individualised risk for depressive symptoms during pregnancy, and therefore includes the collection of information pertinent to risk factors identified in the literature. These will be used in exploratory analyses to determine risk factors which are salient in our understanding and interpretation of the application-derived data.

As described above, a list of risk factors will be used as inclusion criteria, to which prospective participants will be asked to select all those which apply. After enrolment, additional details about particular risk factors of interest will be collected from all participants: adult attachment (Adult Attachment Questionnaire^38^), stressful life events (List of Threatening Experiences^39^) and intimate partner violence (Composite Abuse Scale^40^). Additionally, information will be collected on demographic and obstetrical risk factors such as prior history of pregnancy loss, fertility issues, race, ethnicity and socioeconomic status.

In order to improve accessibility to the study and ensure that research burden is not a prohibitive factor for prospective users who may not be able to commit as much time to the study, some risk factor measures are only to be administered in the opt-in comprehensive subset of the cohort. These include couple satisfaction (Couple Satisfaction Index^41^), childhood trauma (Childhood Trauma Questionnaire^42^), perceived social support (Multidimensional Scale of Perceived Social Support^43^), antenatal attachment (Maternal Antenatal Attachment Scale^44^) and perceived stress (Perceived Stress Scale^45^).

### Biological sample collection

An optional component of the study involves the collection of biological samples, with a particular emphasis on participation from those in the comprehensive cohort. Samples will include blood and saliva, collected at 25 weeks of gestation and again at 2 months postpartum. Participants may choose to provide one or both sample types and will also be invited to consent to the collection of saliva samples from their infants at 2 months postpartum.

Blood samples are ideally scheduled for collection between 12:00 and 15:00 to minimise the effects of diurnal variation on analyte levels. However, samples collected outside this time frame will still be included, and all collection times will be recorded. A trained phlebotomist will obtain two serum tubes, two EDTA tubes and two PaxGene tubes from each participant. Samples will be processed and stored at −80°C for subsequent analysis of serum circulating biomarkers related to stress and pregnancy, including hormones and inflammatory cytokines, as well as for DNA extraction.

At both 25 weeks gestation and 2 months postpartum, participants will be sent the necessary equipment to complete saliva collection at home. Participants will be asked to collect saliva throughout the day to assess diurnal cortisol secretion and the cortisol awakening response, due to evidence of disrupted hypothalamic pituitary adrenal (HPA) axis function in women suffering with AD.^46^ Salivary sampling is often favoured over blood collection for measuring cortisol levels due to its simplicity, low cost and non-invasive nature. Moreover, studies examining HPA axis function have reported a strong correlation between salivary and plasma cortisol concentrations.^47^ Samples will be taken at awakening, at 15, 30 and 60 min post awakening, at midday and at 12:00. Sample collection will involve holding a synthetic swab (Starstedt, Leicester, UK) in the mouth for 2 min. These samples will be posted back to researchers, where they will be frozen at −20°C. For analysis of salivary cortisol concentrations, samples will be thawed, centrifuged at 3000 rpm for 15 min and analysed using a commercially available high sensitivity salivary cortisol enzyme immunoassay kit (Salimetrics).

Where specific consent is given, will also be asked to provide an additional saliva sample for DNA analysis (ORAgene, DNA genotek).

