#### Exploratory objectives

To test the association between physiological biomarkers (obtained from blood and saliva samples collected during pregnancy and the early postpartum) and digital markers collected via the mobile application.To test the association between measures of mother–infant interaction in the early postpartum using the Crittenden Child Adult Relationship Experimental Index (CARE-Index)^23^ and digital markers collected via the mobile application, in the subsample receiving a comprehensive, face-to-face clinical assessment, including a video to assess this.

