### Sample size

Given that this study is conducting exploratory analyses regarding machine-learning-generated predictive values of application-derived datasets, a power calculation was not deemed appropriate. However, instead, the consortium determined approximately 150 participants per recruitment site (1000 in total) to be a feasible recruitment target within the timescales allowed by the consortium work plan, while being large enough to represent the cultural and demographic differences across contexts.

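### Two of the six saliva times coincide at noon, so the written schedule does not support the whole-day cortisol profile it is meant to give

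*Protocol article*

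**What the plan says.** The protocol article, under Biological sample collection, gives the saliva work two aims: "Participants will be asked to collect saliva throughout the day to assess diurnal cortisol secretion and the cortisol awakening response". The same paragraph then fixes the times: "Samples will be taken at awakening, at 15, 30 and 60 min post awakening, at midday and at 12:00". The schedule serves two occasions: "At both 25 weeks gestation and 2 months postpartum, participants will be sent the necessary equipment to complete saliva collection at home".

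The paragraph on blood in that section writes clock times in 24-hour form: "Blood samples are ideally scheduled for collection between 12:00 and 15:00". It allows blood to be drawn outside that window and provides for the time of each draw to be recorded. No matching statement is made for saliva.

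The data feed an exploratory objective: "To test the association between physiological biomarkers (obtained from blood and saliva samples collected during pregnancy and the early postpartum", tested against the digital markers from the app (Exploratory objectives). Sampling is described as optional. Table 1 has no saliva schedule, and no other section gives one.

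**The concern.** The purpose and the schedule stand in the same paragraph and do not match. Midday and 12:00 are listed as two samples but name one time. Read literally, a participant provides two swabs at noon and none in the afternoon or evening, although diurnal secretion is one of the two stated measures.

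At stake is the diurnal part of the cortisol data. A slope or an area over the day needs at least one point late in the day, and a late-day swab that was not taken cannot be recovered afterwards. Sampling is done at home, and Study design says that all sites follow the protocol as described in the article. The wording of this sentence therefore matters in practice, even though the objective is exploratory.

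**Working it through.** The plan gives no figure to reproduce on this point, and no sample-size or power quantity is involved. The check counts the distinct times and compares the span they cover with the stated purpose.

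**Inputs from the protocol article (Biological sample collection)**
- Listed times: awakening, +15 min, +30 min, +60 min, midday, 12:00. That is 6 entries.
- Clock convention: the blood window ends at 15:00, so the clock is 24-hour and 12:00 is noon.
- Occasions: 2 (25 weeks' gestation and 2 months postpartum).

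**Assumptions (not in the documents)**
- Awakening between 06:00 and 09:00.
- A waking day of 16 hours.

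**Step 1: distinct times.** Midday = 12:00, so distinct times = 6 − 1 = 5. One of the six swabs is redundant at each occasion. Over two occasions, 12 swabs give 2 × 5 = 10 distinct points.

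**Step 2: where they lie.** Awakening, +15, +30 and +60 min are four times within the first hour. After that hour there is one time, noon, and nothing later.

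**Step 3: span covered.** Span = 12:00 − awakening time; share = span / 16 h.

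| Assumed awakening | Span to last sample | Share of 16 h | Hours after last sample |
|---|---|---|---|
| 06:00 | 6 h | 6/16 = 37.5% | 16 − 6 = 10 h |
| 09:00 | 3 h | 3/16 = 18.75% | 16 − 3 = 13 h |

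The written schedule thus covers about 19% to 38% of the waking day.

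**Step 4: what can be estimated from the times as written**

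| Measure | Supported? | Reason |
|---|---|---|
| Cortisol awakening response | Yes | Four unambiguous times in the first hour |
| Wake-to-noon change | Yes | Awakening and noon are both present |
| Whole-day slope | No | No point after noon |
| Daytime area under the curve | No | No point in the last 10 to 13 assumed waking hours |
| Evening level | No | No evening sample |

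The conclusion in Step 4 does not depend on the assumed awakening time. Only the percentages in Step 3 do.

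**The case against.** The strongest reply is that this is a misprint and not a design. Nobody plans a six-sample day with two swabs at noon, and the paragraph itself says that collection runs across the day. The full protocol and the instructions sent with the equipment are not shown and may carry a sensible later time. The article also reports extensive training at all sites to reach reliability in data collection. Most of this stands. It explains the error but does not remove it: nothing in the article supplies the right time, and the article is the text that sites are said to follow.

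One could also read 12:00 as midnight. The 24-hour blood window speaks against that, and if midnight was meant, the entry is still wrong as printed.

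Three stronger readings are tempting, and the documents do not support them:
- **That nothing will be collected after noon.** The text shows that the written schedule fails its purpose. It does not show what sites do.
- **That sites will choose different last times and the biomarker analysis cannot be pooled.** This is conjecture. The instructions given to participants are not shown. The four samples in the first hour are unambiguous, so the awakening response is unaffected. Blood hormones and cytokines do not depend on the saliva schedule.
- **That study conclusions are at risk.** The primary outcome is weekly engagement with the app. The secondary objectives concern usability and prediction against standard scales and interview. The four groups of model inputs under Data analyses include no biomarkers.

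**Conclusion.** The concern holds in a limited form. The written schedule contradicts its stated purpose: it has five distinct times and not six, four of them in the first hour, and it ends at noon. It supports the awakening response and a wake-to-noon change but not a whole-day profile.

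That much rests only on the article's own clock convention. The 19% to 38% coverage rests in addition on the assumed awakening times and 16-hour day, and it describes the schedule as printed, not necessarily as carried out. The duplicate is most likely a misprint, and the article does not show which of the two entries is wrong or what was intended.

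The reach is narrow: the diurnal cortisol measure, at both occasions, within an optional component that serves an exploratory objective. The text should still be corrected, because it is an operative sampling rule that fails one of its two aims if followed.

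**What to change.** 1. Reconcile the two coinciding entries with the whole-day purpose and with the instructions in use at all sites, so that the duplicated entry becomes a distinct later-day time. The sponsor has to supply the intended time, since the article does not reveal it.
2. State that the actual time of each saliva sample is recorded, as is already stated for blood.
3. Compute whole-day diurnal measures only for participants with a recorded later-day sample, and report how many these are. The awakening response can be analysed for all who gave the first-hour samples.

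The cost is small: one corrected time in the text, a check against the site instructions and a recorded time for each swab. The number of samples stays at six per occasion.

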### Assessment of mother–infant interaction

Mother–infant interaction will be assessed using the CARE-Index, a reliable and valid coding method used in clinical and research contexts from birth to 15 months. Video interactions will be filmed, and mothers will be instructed to play with their babies as they normally would. Interaction will be assessed across the following dimensions: maternal behaviour, infant behaviour and dyadic synchrony.^23 48^

### Patient and public involvement

The HappyMums consortium has been designed to include the voices of patient representative groups in all aspects of design and implementation. As such, we are grateful to have worked with Tommy’s, a UK-based charity, and the Italian Marcé Society for Perinatal Mental Health, who have provided their own perspective, as well as that of those they work with, at multiple stages in this development process. Surveys were also distributed to potential users (both patients and clinicians) of the app, to gain early feedback during its creation.

### Data analyses

Given the multinational nature of the study, data analyses will be conducted at site-specific and study-wide levels. To address the aim of testing the usage of the app in the at-risk pregnant population, sites will specifically examine their usage data at a site-specific level, before being appraised study-wide. This will be conducted first by developing a set of descriptive analyses to address the primary objective by profiling the proportion of participants who engaged weekly with the mobile application and examining demographic and psychosocial characteristics of active and non-active users, including the antenatal trajectories of depressive symptoms as measured by the EPDS.

Following data completion, study data from all sites will be integrated within a secure federated learning framework to train and evaluate predictive models for maternal depression. This decentralised approach enables sensitive data to remain at local sites while allowing cross-site model training, preserving participant privacy and ensuring diversity in the learnt patterns. Predictive modelling will focus on classifying the risk of AD, as measured by EPDS (Edinburgh Postnatal Depression Scale) scores at baseline, third trimester and postpartum follow-up, with key outcomes defined as binary variables (eg, EPDS ≥13) and continuous trajectories of depressive symptoms over time.

Three supervised machine learning models will be evaluated: Random Forest, Support Vector Machines and logistic regression. These models will be trained on a combination of app-derived and traditional data sources. Input features will be grouped into distinct domains: (1) passive smartphone-derived data (eg, mobility patterns, phone usage, sleep-wake cycles); (2) active self-report data (eg, mood ratings, cognitive performance from app-based tasks); (3) psychosocial and clinical history data (eg, social support, previous mental health diagnoses, adverse life events); and (4) demographic and obstetrical information (eg, age, parity, gestational age, education level).

Model performance will be evaluated using cross-validation techniques within the federated environment. Feature importance will be assessed using internal metrics (eg, Gini importance in Random Forests), and model-agnostic interpretability will be explored via SHAP (SHapley Additive exPlanations) analysis. This will help identify the most influential individual predictors and feature groups contributing to AD risk, aiding interpretability and translational relevance for clinical stakeholders. In doing so, the study aims to provide interpretable, generalisable and privacy-preserving models for early identification and personalised risk assessment of maternal depression.

We acknowledge that there are certain limitations and key risks of this protocol which should be taken into consideration. In terms of data quality and cross-country implementation, we recognise that there is a risk that different languages and cultural contexts could lead to heterogeneity in data collected. To mitigate this, active data collected is in the form of standardised self-report questionnaires which have validated translations. In addition, tasks on the app do not require language input, such as typing speed and voice recognition. Furthermore, researchers on the project have undergone extensive training at all sites to reach reliability in data collection, both online and face-to-face at consortium meetings. As with any study involving the use of technology, we have anticipated technical challenges which could potentially arise, due to different operating systems, phone models and software updates. To mitigate this, the app has been extensively tested by team members at all sites and rounds of feedback have been provided to developers, Ab.acus. The app developers have created in-depth user manuals which will be shared with participants and researchers, to use for troubleshooting, if technical challenges arise. Researchers have trained in guiding participants through any technical errors to ensure smooth usage of the app. As this is a multicentre clinical study, we understand that there might be concern about data sharing and regulations. To mitigate this, a Federated Analysis environment will be developed by the University of Barcelona, whereby models will be trained without data leaving local servers. Furthermore, a Joint Controllership Agreement and Consortium Agreement has been executed by all consortium partners and data collecting sites to ensure ethical use of data. We acknowledge that participants will be completing a battery of self-report measures, which can be burdensome. To mitigate this, a small subgroup, that is, the comprehensive/validation cohort will undergo a more in-depth assessment and will be compensated for their time accordingly. Finally, a current limitation of this methodology is that it excludes individuals who lack access to an appropriate smartphone, who may be part of a deprived demographic group and experience many barriers to care.

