#### Secondary objectives

To assess the usability of the application, the ‘Systems Usability Scale’ and ‘Unified Theory of Acceptance and Use of Technology’ questionnaires will be administered to users after they cease their use of the application (after giving birth).To test the predictive ability of the model, using data passively and actively collected by the application, prediction of antenatal mental health trajectories of users as determined by the app will be compared with standardised measures via the Edinburgh Postnatal Depression Scale (EPDS) and the Patient Health Questionnaire 9 item, available for app users to complete every 2 weeks. A separate subanalysis will be conducted in the subsample receiving a comprehensive, face-to-face clinical assessment with the Mini International Neuropsychiatric Interview (MINI) at baseline and in the early postpartum.

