## Methods and analysis

### Data collection plan

Data will be collected according to the data collection timeline in table 1.

**Table 1 T1:** Timeline of measures

Time point	In app	By researchers
Baseline/enrolment		Demographics, EPDS, PHQ-9, GAD-7, CAS, AAQ
		(Comprehensive/validation subsample only: CSI, MINI, CTQ)
Week 25	Cognitive tasks	(Comprehensive/validation subsample only: MSPSS, MAAS, PSS)
Every 2 weeks	EPDS, PHQ-9, GAD-7	
Week 27	Emotion recognition tasks	
Week 35	Cognitive tasks	(Comprehensive/ validation subsample only: MSPSS, MAAS, PSS)
Week 37	Emotion recognition tasks	
From birth to 2 months postpartum	PHQ-9, GAD-7, EPDS	Birth questionnaire, BLE, SUS, UTAUT (Comprehensive/ validation subsample only: PBQ, CSI, MINI)

AAQ, Adult Attachment Questionnaire; BLE, Brief Life Events; CAS, Composite Abuse Scale; CSI, Couple Satisfaction Index; CTQ, Childhood Trauma Questionnaire; EPDS, Edinburgh Postnatal Depression Scale; GAD, Generalised Anxiety Disorder Assessment; MAAS, Maternal Antenatal Attachment Scale; MINI, Mini International Neuropsychiatric Interview; MSPSS, Multidimensional Scale of Perceived Social Support; PHQ, Patient Health Questionnaire; PSS, Perceived Stress Scale; SUS, Systems Usability Scale; UTAUT, Unified Theory OF Acceptance and Use of Technology.

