#### Data collection

The main aim of the mobile application is to act as a data collection device, which will collect information across a variety of modalities in order to explore which data types are most useful for predicting AD risk and trajectory. The participants will use the app according to their preferences, although notifications will be sent to remind them of specific activities.

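### After baseline the EPDS is scheduled only inside the app, so later EPDS outcomes will be missing in relation to the engagement being studied

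*Protocol article*

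**What the plan says.** Table 1 (Data collection plan) assigns each measure either to the app or to researchers:

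- **Baseline, researchers, all participants:** "Demographics, EPDS, PHQ-9, GAD-7, CAS, AAQ".
- **Every two weeks, in app:** "EPDS, PHQ-9, GAD-7". The researcher column of this row is empty.
- **Weeks 25 and 35, researchers, comprehensive subsample only:** "MSPSS, MAAS, PSS". No depression scale is included.
- **Birth to 2 months postpartum, in app:** "PHQ-9, GAD-7, EPDS".
- **Birth to 2 months postpartum, researchers, all participants:** "Birth questionnaire, BLE, SUS, UTAUT". No EPDS is included. The subsample additionally has the PBQ, CSI and MINI.

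The Secondary objectives agree with the table: the EPDS and PHQ-9 are "available for app users to complete every 2 weeks". Use of the app is voluntary: "The participants will use the app according to their preferences, although notifications will be sent to remind them of specific activities".

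The Data analyses section then uses the EPDS in two ways. The first is descriptive, "examining demographic and psychosocial characteristics of active and non-active users, including the antenatal trajectories of depressive symptoms as measured by the EPDS". The second is as the outcome of the predictive models, at baseline, in the third trimester and postpartum, both dichotomised (for example at 13 or more) and as a continuous trajectory. Model performance is to be judged by cross-validation within the federated environment.

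**The concern.** Completing the in-app EPDS is itself an act of app use. The behaviour that sorts participants into active and non-active therefore also largely decides whether their depression score is seen after baseline. A difference in trajectories between the two groups would mix a difference in mood with a difference in who was still answering.

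The models have the same problem. A third-trimester or postpartum label exists only for someone who opened the app and completed the scale around that time. If worsening mood makes people stop opening the app, missingness depends on the outcome. The fitted risks would then be too low for the at-risk population the tool is meant for. Training and validation folds come from the same observed records, so internal performance figures would give no warning.

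The primary outcome asks what proportion keep using the app weekly, so the study itself treats disengagement as an open question. How missing data are handled can be left to an analysis plan that is not shown. The collection schedule is fixed here, however, and no analysis plan can supply scores that were never collected.

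**Working it through.** The article states no completion rate, dropout rate or expected prevalence, so it has no figure of its own to reproduce. The check compares the schedule with the analyses, followed by arithmetic on labelled assumptions.

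**1. Where each analysed EPDS comes from**

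- Baseline: researchers, everyone. Independent of app use.
- Antenatal trajectory and third trimester: app only. Depends on app use.
- Postpartum: app only. Depends on app use after birth, beyond the pregnancy window in which the primary outcome measures engagement.

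**2. What a non-active user can still contribute**

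I take active to mean the at-least-weekly use of the primary outcome; the Data analyses section does not define it separately. Fortnightly EPDS occasions = (40 − gestation at enrolment) / 2, rounded down. Delivery at 40 weeks is an assumption; enrolment at 13 to 28 weeks is from the Participants section.

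- Week 13: 27 / 2, giving 13 occasions
- Week 20: 20 / 2 = 10 occasions
- Week 28: 12 / 2 = 6 occasions

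Someone who opens the app every second week fails the weekly criterion but can fill every occasion. Someone who stops late has a truncated series. Someone who never uses the app has the baseline score alone.

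**3. App-independent information after baseline**

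The Recruitment process section sets the opt-in comprehensive cohort at a minimum of 30 per site: 7 × 30 = 210, or 210 / 1000 = 21% of the planned sample. These participants have a MINI at baseline and after birth. It is not an EPDS and gives no antenatal trajectory.

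**4. Illustration of outcome-dependent missingness (all inputs assumed)**

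Let p be the true prevalence of EPDS of 13 or more, and rD and rN the completion rates in depressed and non-depressed participants. Observed prevalence = p·rD / [p·rD + (1 − p)·rN]; share missing = 1 − [p·rD + (1 − p)·rN]. With p = 0.30:

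- rN = 0.6, rD = 0.4: 0.12 / (0.12 + 0.42) = 0.12 / 0.54 = 22.2%; 46% missing
- rN = 0.6, rD = 0.5: 0.15 / (0.15 + 0.42) = 0.15 / 0.57 = 26.3%; 43% missing
- rN = 0.5, rD = 0.3: 0.09 / (0.09 + 0.35) = 0.09 / 0.44 = 20.5%; 56% missing

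Under this mechanism the odds of the outcome are multiplied by rD / rN, which is 0.4 / 0.6 = 0.67 in the first case. Predicted risks are shifted downwards accordingly. Sensitivity, specificity and the AUC do not change, because the predictor distribution within each outcome class is untouched.

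**5. Bounds that assume nothing about the mechanism**

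If a share e of participants has the later EPDS and 30% of those score 13 or more (both assumed), the true prevalence lies between 0.30·e and 0.30·e + (1 − e):

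- e = 0.9: 0.27 to 0.37
- e = 0.7: 0.21 to 0.51
- e = 0.5: 0.15 to 0.65
- e = 0.3: 0.09 to 0.79

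**The case against.** The strongest reply is that much of the study is untouched. The primary outcome is measured from usage. The trajectory comparison is one element of a descriptive set, and the Sample size section describes the modelling as exploratory. Prevalence of EPDS of 13 or more is not a stated objective. Reminders are sent, and a dashboard lets the study team see data entry, so lapses are visible. The post-birth MINI lies outside the app and was included to assess its validity. All of this stands and limits the weight of the point. It does not close the gap: reminders and the dashboard act through the app or on observation alone, and the MINI subsample is self-selected.

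A reader might infer that non-active users have no trajectory at all. The documents do not support that. The engagement criterion is weekly while the EPDS is fortnightly, so non-active users can have partial or even complete series.

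A reader might also infer that the model outcome exists only for people who stayed engaged. That is too strong as well. Baseline EPDS is a named outcome time point scheduled for everyone, and a later value needs one completion near that time rather than sustained weekly use.

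A further reply is that an off-app score from someone who abandoned the app adds an outcome without concurrent app predictors. This is partly right. However, anyone who used the app in pregnancy and stopped after birth has the predictors and lacks only the label, and the psychosocial, clinical-history and demographic inputs do not all depend on the app.

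**Conclusion.** The point holds in a limited form. After baseline the EPDS is scheduled only inside the app, so non-active users' series will tend to be sparse or truncated, and third-trimester and postpartum model outcomes will be missing in relation to engagement. This can bias the active versus non-active comparison and the models' calibration and generalisability, without internal validation showing it.

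The size cannot be fixed from the article. On the assumed figures, a true prevalence of 30% is observed as 20.5% to 26.3%, with 43% to 56% of outcomes missing. Without an assumption about the mechanism, an observed 30% with half the outcomes seen is compatible with 15% to 65%. The direction in the first illustration rests on depressed participants completing less often, which is plausible but not documented.

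Biased discrimination is a tempting further conclusion, but it is not shown: where missingness depends on outcome status alone, the AUC is unchanged. It could move if missingness also depended on the predictors within outcome classes, but nothing in the article allows that to be sized.

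This is a cheap and worthwhile improvement to data collection. It does not threaten the primary outcome.

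**What to change.** - **Postpartum:** add the EPDS to the researcher contact between birth and 2 months that already collects the birth questionnaire, BLE, SUS and UTAUT. Collect it from every enrolled participant whatever their app use, and use that score as the postpartum model outcome.
- **Third trimester, where feasible:** send an off-app EPDS link once to participants with no recent in-app EPDS.
- **Analysis and reporting:** keep all in-app EPDS data in the active versus non-active comparison, since restricting it to baseline would discard valid serial scores. Report EPDS completeness by engagement group, and state that antenatal trajectories are conditional on app use.

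The cost is one more short questionnaire per participant at a contact that already exists. The third-trimester link costs more: researcher measures at week 35 are scheduled only for the comprehensive subsample, so for everyone else it is a new contact. It could also prompt app use and so touch the primary outcome; such contacts should be logged. Antenatal scores not collected at the time cannot be recovered later, so the change is worth most if made while participants are still being followed.
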